## Methods/design

### Study design

We are performing a single-centre, two-arm, parallel, prospective RCT comparing an exercise program using HIIT against standard preoperative care for patients undergoing major abdominal surgery.

### Recruitment to the study

The study is being performed at Dunedin Public Hospital, which is a tertiary care university hospital servicing a large geographical area in the south of New Zealand.

All patients we identify as fulfilling the inclusion criteria are being invited to participate in the study.

The inclusion criteria are:patient requiring major abdominal surgery;aged 45–85 years;able to attend multiple supervised exercise sessions at the hospital;available during a 4–6-week window up to the time of the confirmed surgery.

The definition of major abdominal surgery is any abdominal procedure expected to last 2 h or with an anticipated blood loss > 500 mL [28]. This included all gastrointestinal resections, liver surgery, large abdominal wall hernia repairs, abdominal aortic aneurysm repair, hysterectomy, radical prostatectomy and nephrectomy. For the purposes of this study, procedures such as laparoscopic cholecystectomy or transurethral resection of the prostate are not considered to be major abdominal surgery.

The exclusion criteria are related to medical risk factors and to conditions or treatments which could independently alter the Peak VO_2_ in the weeks before surgery. These include:inability to exercise or to perform a CPET;contraindication to exercise found on CPET;uncontrolled hypertension (blood pressure > 180/100);experiencing clinical angina (this does not include patients with a history of ischaemic heart disease who have no symptomatic angina on appropriate medical treatment or those who have previously had a successful revascularisation procedure);myocardial infarction in the past three months;uncontrolled cardiac arrhythmias;aortic aneurysm > 6.5 cm;severe obstructive pulmonary disease with a FEV1 < 1.0 L;inability to provide consent;significant anaemia defined as a haemoglobin level < 80 g/L or being on a treatment which would increase the haemoglobin in the 4–6 weeks before surgery;preoperative chemotherapy during the 4–6 weeks before surgery; orshort course preoperative radiotherapy.

Protocol amendment number 01 was introduced in 19 April 2016 and increased the acceptable range for the age and the blood pressure of participants in the study to the levels listed above.

### Participant progress through the study

The study design is outlined in Fig. 1. In terms of patient care, all eligible participants have been assessed by their surgical team and by the hospital’s anaesthetic preassessment clinic. Potential participants for the study are identified when they are booked onto a list (with a specific date) for their operation. Those who are 4–6 weeks out from surgery, who live in or around Dunedin, and do not have any obvious exclusion criteria are contacted by the research nurse. Those who are interested are then invited to visit the hospital. Following discussion about the aims of the study and familiarisation with the study protocol, the participant is given written information about the study, is interviewed by the research nurse and is assessed by the study’s anaesthetist. When all questions are answered, and if there are no exclusion criteria, consent is obtained by the research nurse and the first cardiopulmonary exercise test (CPET) is performed. Baseline clinical data obtained before the CPET test includes full clinical history and examination, investigations done as part of the participant’s preoperative workup, up-to-date vital signs and a SF-36 quality of life score. The results of the CPET test are checked by a cardiologist and following this the participant is accepted into the study and randomly allocated 1:1 to standard care or to the exercise training group by the exercise physiologist. Randomisation was performed in blocks of unequal length (equal probabilities of 2, 4 and 6 lengths), using computerised sequence numbers generated in Stata, with no stratification. The allocation code is kept in sealed opaque envelopes which are sequentially opened. The allocation sequence was generated by the study statistician who has no involvement in the enrolment, assignment or assessment of participants. The enrolment of patients is coordinated by the research nurse. The number of patients approached, those excluded and those who declined to be involved (with reasons given for this) is also being documented as it the participant’s preference for exercise training or normal care.

**Fig. 1 Fig1:**
[figure not shown]
Study design

### Interventions

Cardiopulmonary exercise testing (Quark CPET; Cosmed, Rome, Italy. Integrated gas analysis – Quark B2, integrated ECG analysis Quark C12) is performed in all participants while pedalling a stationary cycle ergometer (Quark Ergoline) immediately before randomisation and again before surgery. Before each test the metabolic analysers are calibrated as per the manufacturer’s recommendations. The oxygen (O_2_) and carbon dioxide (CO_2_) analysers were calibrated using a two-point calibration room air and a standardised gas containing 15% O_2_ and 6% CO_2_. The gas turbine was calibrated using a 3-L syringe (known volume) as instructed by the manufacturer. If the calibration failed, it was repeated until successful (software autocorrects if values fall below 5% error) before beginning the test. The test is performed in the hospital by two clinical researchers. After 3-min resting (for resting spirometry and to let gas exchange variables stabilise), the test proceeds with 2-min stages against an incremental resistance until termination, followed by 5 min of active recovery. Initial workloads were set at 25–50 W and stages increased by 10–50 W based on the participant’s fitness level and heart rate response. Heart rate, 12-lead electrocardiogram, blood pressure, and rated perceived exertion (RPE) are monitored throughout the procedure. The test was terminated when the participant had made a maximal effort (had reached volitional exhaustion). Additional evidence to support a good quality test included a respiratory exchange ratio (RER) of ≥ 1.1 or a plateau in the VO_2_ with increasing workload. If a participant terminates the test without reaching an RER of ≥ 1.1 this will be noted in the results. Additional medical reasons for terminating the test are discussed under safety. Other measures documented during CPET include the anaerobic threshold, resting and maximal heart rate (HRmax), blood pressure, the maximal workload in watts and the workload required to elicit 60% and 90% HRmax.

Participants are randomised either to standard care or exercise. Standard perioperative care at our hospital includes an anaesthetic preassessment clinic, a visit to the hospital with an orientation to enhanced recovery after surgery (ERAS) targets, a tour of the wards, treatment of anaemia, advice on stopping smoking and encouragement to exercise. However, as our institution has no staff with dedicated time for ‘optimising patients’ preoperatively there is no ability to follow up on advice given, especially with respect to exercise. For those randomised to ‘exercise’, the protocol is for 14 sessions of HIIT over 4–6 weeks. The frequency of sessions will be adjusted according to the number of weeks available, so that participants complete three or four sessions a week with the aim of completing their HIIT sessions three days before their scheduled surgery. The HIIT program uses stationary cycling on an electronically braked cycle ergometer (Monark Ergomedic 828E) and is performed under the supervision of a trained exercise physiologist. Each session begins and ends with 5 min of cycling against a light load. The frame work of the protocol is to start with ten 1-min intervals of intense exercise with the goal of reaching heart rates > 90% of HRmax with alternating ‘rest’ intervals of lower intensity cycling lasting 1 min at heart rates of ≥ 60% maximum heart rate. The duration of intense exercise intervals will increase as the participant gains fitness, with an aim of participants achieving five 2-min intervals of high intensity work with each high intensity interval being followed by 1–2-min of lower intensity cycling. During HIIT participants will alter the intensity of their exercise by manually adjust the resistance on their ergometers. This is reduced during periods of lower intensity cycling and is increased during periods of intense exercise to help achieve the target heart rate of 90% HR max. HRmax is defined as 220-age. The training programs will be individualised to the target heart rate and the performance of the participant. In this context, the protocol allows for individualised adjustments to accommodate patients with multiple co-morbidities. In these participants, the period of intense exercise will proceed for a time period that is reasonably tolerated (anywhere between 15 s to 1 min), followed by a period of lower intensity cycling for approximately 1 min. We would aim for this sequence to be repeated ten times. The duration of the intervals of intense exercise is then increased as tolerated in subsequent exercise sessions. In contrast, participants who are physiologically fit may rapidly increase the duration of intense exercise up to 4-min intervals. The total intense interval duration will not exceed 10 min throughout the training period. The training sessions, including warm up and cool down, last approximately 30 min. The impact of associated co-morbidities on the individualisation of the HIIT program will be noted. For patients on beta blockers, the level of perceived exertion, using the 6–20 Borg scale [29], will be monitored as well as the pulse, with a perceived exertion score of 18 being used as a substitute of 90% of HRmax. For safety reasons, the intensity of exercise and intervals will be adjusted if the heart rate exceeds 95% of the maximum observed on the baseline CPET or if the perceived exertion on the Borg scale exceeds 18. The pulse, as an indicator of ‘high intensity’ targets being reached, will be monitored and recorded from downloadable Polar Heart Rate monitors to ensure exercise adherence. This will be monitored by the exercise physiologist and the information is used to help with adjusting subsequent exercise sessions. Any patient who develops an AE will be clinically assessed and will be reported to the safety monitoring committee. All AEs will be reported with the results of the study. Patients who have their surgery delayed will complete one additional HIIT session per week up until surgery to maintain fitness [30, 32]. Adherence will be measured by the number of HIIT sessions attended and the number of sessions where a target HR of > 90% was reached.

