
### Outcomes

The primary outcome of our study is the change in Peak VO_2_. The peak VO_2_ is defined as the mean of the highest two rates of oxygen consumption measured during CPET [31]. This is documented after randomisation and again before surgery in all participants. One reason for measuring Peak VO_2_ a second time in the control group is that it enables us to identify any improvement in performance at the second CPET associated with becoming more familiar with the cycle ergometer.

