### Blinding

For the primary endpoint, Peak VO_2_, as the exercise physiologist supervises both the CPET test and the HIIT exercise program, he is not blinded. The Peak VO_2_ is measured at the point of maximal effort, which is reached with the encouragement of two independent researchers. In terms of secondary endpoints, the documentation of complications and administration of the questionnaires is performed by the principal investigator and a research assistant who are blinded to the group the patient has been randomised to. The study statistician will use non-informative study codes and remains blinded as to the actual allocation groups until all primary analyses are completed.

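### Peak VO2 depends on effort, its second test is supervised unblinded, and the workload settings are not tied to the first test, so test conduct could add to or mask the HIIT effect

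*Protocol article*

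**What the plan says.** Under Outcomes, the protocol article states: "The primary outcome of our study is the change in Peak VO_2". Peak VO2 is defined there as the "mean of the highest two rates of oxygen consumption measured during CPET".

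Under Interventions, the test runs in 2-minute stages of rising resistance until volitional exhaustion. The load rule is: "Initial workloads were set at 25–50 W and stages increased by 10–50 W based on the participant’s fitness level and heart rate response". The paragraph covers both tests, one around randomisation and one before surgery. An RER of at least 1.1, or a VO2 plateau, counts as additional evidence of a good test. On tests that miss the RER mark it says: "If a participant terminates the test without reaching an RER of ≥ 1.1 this will be noted in the results".

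Under Blinding, the article says openly that "as the exercise physiologist supervises both the CPET test and the HIIT exercise program, he is not blinded". It adds: "The Peak VO_2_ is measured at the point of maximal effort, which is reached with the encouragement of two independent researchers". Blinding is described for complications, for questionnaires and for the statistician, but not for the primary endpoint. Under Participant progress through the study, patients are "randomly allocated 1:1 to standard care or to the exercise training group by the exercise physiologist", so the same role allocates, trains and supervises the test.

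**The concern.** An effort-limited maximum depends on how the test is run as well as on fitness. Three features of the plan leave its conduct open to influence by arm at the second test:

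- the supervisor knows the arm and has trained one of the two groups;
- the load rule refers to fitness, which is what the intervention is meant to alter, and no statement holds the settings constant;
- a test that misses the RER mark is flagged, with no stated consequence.

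A between-arm difference arising at the second test goes straight into the estimated HIIT effect. Adjustment for baseline Peak VO2, as planned under Statistical methods for analysis of endpoints, cannot remove it. A blinded statistician cannot either, because the values have already been produced by then.

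**Working it through.** The article states no standard deviation, power or final sample size, so there is no figure to reproduce. The check is mainly a reading of the text.

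**1. Which test is exposed.** Participant progress and Interventions place the first test before randomisation, which would leave only the second exposed. Outcomes says the measurement is documented after randomisation. These passages must be reconciled; if Outcomes is right, both tests are exposed.

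**2. Which safeguards reach the problem.**

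- Calibration before each test protects the gas analyser, not effort or load settings.
- The two encouraging researchers are called independent. The article does not say whether they know the arm.
- The control-arm retest is offered as a check on familiarity with the ergometer. It cannot separate training from unequal familiarity (the HIIT arm has up to 14 supervised cycling sessions) or from unequal encouragement.
- The RER note identifies tests. The per-protocol rules (ten or more sessions for HIIT, no substantial higher-intensity exercise for controls) contain no test-quality criterion.

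**3. Illustrative size.** Let p be the share of second tests that read low in an arm and d the mean shortfall among them. The bias in the HIIT-minus-control contrast is

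bias = p(control) × d(control) − p(HIIT) × d(HIIT).

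Neither p nor d is in the article. All values below are assumptions.

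| Scenario | Bias (mL/kg/min) | Share of the 2 mL/kg/min target |
|---|---|---|
| Controls only, 10% of tests, 1.0 low | 0.1 × 1.0 = 0.10 | 0.10/2 = 5% |
| Controls only, 20%, 1.5 low | 0.2 × 1.5 = 0.30 | 15% |
| Controls only, 30%, 2.0 low | 0.3 × 2.0 = 0.60 | 30% |
| Same share and shortfall in both arms | 0 | 0% |
| HIIT only | −0.10 to −0.60 | −5% to −30% |

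Only the net difference between arms matters, and its sign can go either way.

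**4. What such a bias does to the test.** Take a target of 2, two-sided 0.05 (both from the article), and assumed 80% power with assumed SDs of change of 2, 3 and 4. The standard formula n = 2(1.96 + 0.84)²SD²/2² gives 16, 36 and 63 per arm. With SE = SD√(2/n), the rejection probability at a net difference b is

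1 − Φ(1.96 − b/SE) + Φ(−1.96 − b/SE).

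For SD 3 and n = 36, SE = 3√(2/36) = 0.707.

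- No true effect, b = 0.25: about 6.4% rejections instead of 5%.
- No true effect, b = 0.5: about 11%.
- True effect 2, masked by 0.5, so b = 1.5: about 56% instead of 80%.

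SDs of 2 and 4 at their own sample sizes give nearly the same figures. At the 90%-power sizes (22, 48 and 85 per arm), the first two become about 7% and 13%.

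**The case against.** The strongest reply is that the article discloses the unblinded supervision, adds partial safeguards, and may leave retest settings and the handling of low-RER tests to the full protocol or the analysis plan. Much of this stands, and several stronger readings should not be drawn:

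- **That loads are chosen afresh at the second test.** The wording permits this but does not say it, and the full protocol may hold the settings fixed.
- **That everyone giving encouragement knows the arm.** This is stated only for the physiologist.
- **That submaximal tests are kept as valid.** A test below RER 1.1 may still be maximal, since exhaustion is the stopping criterion and a plateau also counts. The article does not say how such tests enter the analysis.
- **That disappointed controls try less, so the effect is inflated.** The Discussion reports two reactions to allocation to standard care: taking up one's own exercise, and withdrawal (twice so far). It reports nothing about effort on the test. The first reaction would raise control-arm fitness and shrink the contrast.
- **That the bias has a known size.** Every magnitude here is assumed, and the article does not say how far Peak VO2 moves with load settings.

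The reply does not dispose of the point. The article itself states a load rule based on fitness, unblinded supervision of an effort-limited endpoint, and noting as the only stated response to a low RER. The concern is with what is fixed, and how a second test was run cannot be repaired at the analysis stage.

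**Conclusion.** The point holds in limited form. The primary endpoint depends on effort, is supervised by the unblinded trainer, and uses a load rule that does not tie the second test to the first. Differences between arms in conduct or effort could add to the HIIT effect or mask it. The documents establish neither direction nor size. The 0.1 to 0.6 mL/kg/min range (5% to 30% of the target) and the rejection rates rest wholly on assumed shares, shortfalls, SDs and power. This is a worthwhile, inexpensive improvement, not evidence that the result will be wrong.

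**What to change.** 1. Repeat each participant's first-test start workload and step size at the second test. Leave the medical termination criteria as they are.
2. Have Peak VO2 and anaerobic threshold derived from the exported gas-exchange file by the research assistant who is already blinded for the secondary endpoints. The statistician should not do this, because Participant progress keeps that role out of participant assessment. Data management stores test results in the same folder as the HIIT session records, so the export must be supplied without that folder.
3. Add a supportive sensitivity analysis of the primary model in pairs where both tests reached RER 1.1 or a plateau. Acknowledge that this selects on a post-randomisation variable and so cannot replace the main analysis.
4. Report change in anaerobic threshold with the same model as a supportive outcome. It is already recorded, and the safety section treats it as a point short of peak.
5. Reconcile the statements on whether the first test precedes or follows randomisation.

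The cost is a short test instruction, some staff time and analysis wording; no visits or measurements are added. Some second tests may last longer. Participants already tested keep the existing procedure, so the trial will contain both. Blinded derivation does not remove differences in effort or encouragement, and the report should state that limitation.

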
### Outcomes

The primary outcome of our study is the change in Peak VO_2_. The peak VO_2_ is defined as the mean of the highest two rates of oxygen consumption measured during CPET [31]. This is documented after randomisation and again before surgery in all participants. One reason for measuring Peak VO_2_ a second time in the control group is that it enables us to identify any improvement in performance at the second CPET associated with becoming more familiar with the cycle ergometer.

We selected a range of secondary outcomes to assess the potential impact HIIT may have on patient wellbeing, recovery from surgery and a range of clinical outcomes. Although the study is not powered for these endpoints, we hope to gain sufficient information about them to assist with the design of subsequent studies. The two traditional clinical outcome endpoints that we are assessing are the length of hospital stay and postoperative complications. The length of stay is the number of postoperative days stayed in hospital, with day 1 being the day of surgery. Postoperative complications, using standard definitions [32, 33], are documented in hospital and after discharge. Complications in hospital will be prospectively identified by visiting the patient in the ward and from the patient’s medical records. The patient will then be contacted by a member of the research team six weeks after surgery. A previously validated questionnaire [1] is used to identify complications that developed after discharge from hospital. We are also documenting three composite postoperative scores. The postoperative morbidity survey (POMS) assesses postoperative adverse events in nine different categories according to predefined criteria that are easy to check and to document [34]. This gives an excellent overview of postoperative morbidity [28] and may give a more comprehensive overview of postoperative difficulties than identifying specific postoperative complications. The questionnaire is performed on postoperative day 5, either by direct interview in the ward or by telephone if the patient has been discharged. In contrast, the surgical recovery scale (SRS) is designed to look specifically at recovery after surgery. This assesses 13 items including energy levels, feeling of fatigue and a number of practical physical activities, and correlates well with major complications and length of hospital stay [35]. The SRS will be performed on postoperative day 5 and will be repeated at six weeks as a postal questionnaire. Third, we are documenting the quality of life using the short form 36 health survey (SF-36). In the context of this study, the SF-36 has two purposes. The first is as a quality of life measurement tool to assess the impact of HIIT on the patients’ overall wellbeing. The second is to assess if there are any differences in physical function after surgery, which can be assessed by using the ten questions which make up the physical functioning component of the score. On the first occasion the SF-36 is completed it will be performed with the patient. On subsequent occasions it will be completed as a postal questionnaire.

### Data management

The schedule for data collection is summarised in the SPIRIT figure (Fig. 2) and checklist. The same dataset is collected for those randomised to exercise or to standard care. Each participant has a folder for demographic data, initial assessment and secondary endpoint results, and a separate folder for CPET results, details of the HIIT exercise program, including sessions attended and adherence to target heart rates. Folders are identified by the participant’s non-informative study number. Electronic data, for example for calculating SF-36 scores, will also be indexed by the participant’s study number and will be stored in a password-secured computer.

